## Abstract

**Background:**

Hodgkin’s lymphoma (HL) and anaplastic large-cell lymphoma (ALCL) are the two most common tumors expressing CD30. Internationally, a clinical study that is being conducted involving adults with recurrent or refractory HL or ALCL suggests efficacy of brentuximab vedotin (SGN-35). Pediatric patients should be given medicines that have been appropriately evaluated for their use. In the past, however, new approved drugs have been used for pediatric patients without the confirmation of safety and efficacy in pediatric patients. Therefore, it is important to examine the safety and efficacy of SGN-35 in Japanese children.

**Methods:**

Phase I clinical study of SGN-35 involving children with recurrent or refractory CD30-positive Hodgkin’s lymphoma or systemic anaplastic large cell lymphoma (BV-HLALCL study) is being conducted for pediatric patients in order to evaluate the safety, feasibility and preliminary clinical effectiveness of brentuximab vedotin. SGN-35 is intravenously administered on Day 1 of each cycle (21 days/cycle). The dose of SGN-35 is calculated based on the body weight at the baseline. The primary endpoint is dose limiting toxicity and incidence of adverse events. The secondary endpoints are pharmacokinetics, response rate, complete remission rate, response duration, progression-free survival and event-free survival. The reduction rate of tumor will be calculated according to revised response criteria for malignant lymphoma for measurable tumor. Six pediatric patients will be enrolled in this study.

**Discussion:**

This study aims to expand indication of SGN-35 in Japan by assessing its safety and efficacy in pediatric patients.

**Trial registration:**

JMACCT ID: JMA-IIA00229. Registered on 17 Nov 2015.

## Background

Hodgkin’s lymphoma (HL) and anaplastic large-cell lymphoma (ALCL) are the two most common tumors expressing CD30. The treatment of HL and ALCL has largely relied on cytotoxic chemotherapy.

Basic treatment for childhood HL consists of chemotherapy and low-dose involved field radiotherapy (LD-IFRT). Chemotherapy alone or a combination of chemotherapy and LD-IFRT is selected in accordance with individual children. Furthermore, the intensity of initial chemotherapy is determined based on early treatment responsiveness in order to avoid unnecessary additional chemotherapy or radiotherapy. Chemotherapeutic regimens and treatment schedules differ among clinical studies. In Japan, treatment has not been standardized, and is selected based on the results of international clinical studies in accordance with individual patients. In a representative clinical study regarding childhood HL, the GPOH-HD-2002 study, chemotherapy with vincristine, etoposide, prednisolone, doxorubicin, cyclophosphamide, and procarbazine and LD-IFRT for some patients improved the 5-year event-free survival rate to 89%, and the 5-year survival rate to 97% [1]. In Japan, this treatment is selected for many patients. Treatment for patients with treatment resistance/relapse, accounting for approximately 10% of those with childhood HL, has not been standardized. Patients with local relapse after initial treatment for a low-risk group may be saved by chemotherapy and LD-IFRT, but the exacerbation-free survival rate ranges from 30 to 65% in other patients with treatment resistance/relapse even when hematopoietic cell transplantation is performed [2, 3].

As standard treatment for childhood ALCL, ALCL99, of which the efficacy and safety were confirmed in an international cooperative clinical study involving Europe and Japan, is selected. It refers to combination chemotherapy with dexamethasone, cyclophosphamide, high-dose methotrexate, ifosfamide, etoposide, cytarabine, and doxorubicin. In 352 patients enrolled in the study, the 2-year event-free survival rate was 74.1%, and the 2-year survival rate was 92.5% [4]. There were no marked differences in the results among countries participating in the clinical study. Although the results of initial treatment for childhood ALCL are favorable, it is necessary to arrange treatment for a high-risk group (proportion: approximately 20%) and patients with relapse (proportion: approximately 30%). Retrospective studies suggest the efficacy of allogeneic hematopoietic stem cell transplantation for treatment-resisting patients with progression early after the start of initial treatment and those in whom relapse is frequently detected despite their responses to chemotherapy [5, 6]. Furthermore, another study suggests the efficacy of monotherapy with vinblastine for patients with relapse [7]. However, an optimal treatment period has not been established, and long-term treatment is conducted in many cases.

Although the results of initial treatment for childhood HL and ALCL are favorable, it is necessary to arrange treatment for patients with relapse or refractory. Targeted lymphoma therapy, using an anti-CD30 antibody, provides an innovative treatment modality for specific lymphomas, particularly HL and ALCL.

Brentuximab vedotin (SGN-35) is a new antibody-drug conjugate (ADC) that binds to a cell surface marker, CD30, manufactured by Seattle Genetics, Inc. (SG, Inc.). CD30 is a type 1 membrane-penetrating protein, belonging to the tumor necrosis factor receptor super family. It appears on the Reed-Sternberg cells of HL patients and T cells of those with ALCL or other T-cell-mediated lymphoproliferative diseases.

SGN-35 consists of 3 components: (i) anti-CD30 monoclonal antibody (cAC10), (ii) a potent microtubule inhibitor, monomethylauristatin E (MMAE), and (iii) a linker decomposed by protease. A covalent bond between cAC10 and MMAE is mediated by this linker. The biological activity of SGN-35 appears through the following steps: initially, when SGN-35 binds to CD30 on the tumor cell surface, it is transported to lysosome through intracellular uptake as ADC-CD30 complex. Subsequently, MMAE is released in the intracellular area through protein-decomposing reactions. MMAE binds to tubulin, destroying an intracellular microtubular network and inducing the arrest of the cell cycle. As a result, apoptosis of CD30-expressing tumor cells occurs.

Internationally, a phase I study of SGN-35 (SG035–0001 study) involving patients with recurrent or refractory CD30-positive hematopoietic organ tumors was conducted by SG, Inc. from November 2006 [8]. Thereafter, a phase II study (SG035–0003 study) involving patients with recurrent or refractory CD30-positive HL after autologous hematopoietic stem cell transplantation was conducted from February 2009 [9], and another phase II study involving patients with recurrent or refractory CD30-positive systemic ALCL (sALCL) (excluding those with primary dermal ALCL localized in the skin)(SG035–0004 study) was performed from June 2009 [10]. SGN-35 was approved as ADCETRIS (proprietary name) to be indicated for HL and sALCL patients in August 2011 in the United States and in October 2012 in European Union.

In Japan, a phase I/II study (TB-BC010088 study) involving patients with recurrent or refractory CD30-positive HL or sALCL was conducted by Takeda Bio Development Center Limited from October 2011 [11]. Based on the results of the TB-BC010088, SG035–0003, and SG035–0004 studies as the main studies, a new drug application of SGN-35 was submitted by Takeda Pharmaceutical Company Limited. SGN-35 (proprietary name: ADCETRIS) was approved for patients with recurrent or refractory CD30-positive HL or ALCL. The administration method/dosage is as follows: for adults, brentuximab vedotin (gene recombinant) at 1.8 mg/kg (body weight) should be intravenously infused every 3 weeks. If necessary, the dose should be decreased in accordance with the patient’s condition.

Clinical studies involving adults with recurrent or refractory HL or ALCL in Japan and other countries demonstrated the efficacy and safety of SGN-35. Internationally, a clinical study that is being conducted involving adults with recurrent or refractory HL or ALCL suggests its efficacy. Pediatric patients should be given medicines that have been appropriately evaluated for their use. In the past, however, new approved drugs have been used for pediatric patients without the confirmation of safety and efficacy in pediatric patients. Therefore, it is significant to examine the safety and efficacy of SGN-35 in Japanese children.

In TB-BC010088 study involving Japanese adults [11], dose escalation was started from 1.2 mg/kg. In this dose level, no dose-limiting toxicity (DLT) was observed. In C25002 study involving non-Japanese children [12], dose escalation was started from 1.4 mg/kg. In this dose level also, no DLT was observed. From these results, we omitted dose escalation started from lower than 1.8 mg/m2. The maximum tolerance dose (MTD) of this drug was clarified as 1.8 mg/kg with good efficacy in SG035–0001 clinical study involving adult patients [8]. Therefore, we omitted consideration for more than 1.8 mg/kg dose. From the above, we adopted the design considering only a single dose of 1.8 mg/kg in this study.

## Methods/design

### Protocol digest of the study

#### Objectives

Primary objective is to examine the safety and tolerance of SGN-35 in children with recurrent or refractory CD30-positive HL or sALCL. Accessory objective is to investigate the pharmacokinetics and efficacy of SGN-35 in children with recurrent or refractory CD30-positive HL or sALCL.

#### Study setting and protocol review

This is a single-arm, open-label, multicenter phase I study involving four institutions: Hokkaido University Hospital, St. Marianna University School of Medicine Hospital, National Hospital Organization Nagoya Medical Center, and Kyushu University Hospital. The protocol has been reviewed and approved by institutional review boards of each institutions.

#### End points

<Primary endpoints>(i)DLT(ii)Adverse events

<Secondary endpoints>(i)Pharmacokinetics (serum concentration of SGN-35, plasma concentration of MMAE, and serum concentrations of all antibodies)(ii)Overall response rate (ORR)

ORR refers to the proportion of subjects with complete remission (CR) or partial remission (PR) as the best comprehensive response in analysis set.(iii)Complete remission rate

CR rate refers to the proportion of subjects with CR as the best comprehensive response in analysis set.(iv)Response duration

The response duration refers to a duration from the first day of CR or PR evaluation until the first day of progressive disease (PD) evaluation or the day of death related to some factor (earlier). With respect to data on the response duration in subjects continuing to participate in this study until analysis without PD, those receiving anti-tumor treatment other than the test regimen and stem cell transplantation, and those excluded from this study before CR or PR achievement, the final day of image assessment on which disease progression is ruled out in lesions to be measured is regarded as the day of censoring.(v)Progression-free survival (PFS)

PFS refers to a period from the first day of administration until the first day of PD evaluation or the day of death related to some factor (earlier). With respect to data on PFS in subjects who continued study participation until analysis without showing PD, those who received anti-tumor treatment other than test treatment and stem cell transplantation, and those excluded from this study before CR or PR evaluation, the last day of image assessment on which disease progression was ruled out in lesions to be measured is regarded as the day of censoring. Subjects in whom image assessment after initial administration was not conducted, is censored at day 1.(vi)Event-free survival (EFS)

Events include death, progression of disease, secondary cancer, and toxicity-related discontinuation. Toxicity-related discontinuation refers to the discontinuation of this clinical study related to adverse events of which the relationship with this drug cannot be ruled out. EFS refers to the interval from the first day of administration until the earliest day of event appearance. If there are no events, the subject is censored at the final day of observation. If it is discontinued due to transplantation or withdrawal in the absence of events, they are censored at the day of study discontinuation. If subjects receive new anti-tumor treatment other than stem cell transplantation, they are censored at the start of the treatment.

The anti-tumor effects of SGN-35 are evaluated only in patients with measurable lesions according to the Revised Response Criteria for Malignant Lymphoma [13].

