
### Treatment methods

SGN-35 is intravenously administered on Day 1 of each cycle (21 days/cycle). After Cycle 2, SGN-35 should be administered − 1 to + 3 days from the established day of administration, excluding cases in which a specific duration is required to achieve recovery from toxicity, appearing from the preceding cycle of SGN-35 therapy, of which the association with the investigational drug cannot be ruled out.

The drip infusion time of SGN-35 is ≥30 min. Rapid intravenous injection or bolus administration should be avoided. SGN-35 should be administered using a special line for drip infusion. It must not be mixed with other drugs. When administering SGN-35, the line for drip infusion should be washed in physiological saline (Japan Pharmacopeia) before and after SGN-35 administration so that this drug may not be mixed with other drugs.

The dose of SGN-35 is calculated based on the body weight at the baseline, and expressed as an integral number by rounding the first decimal place. In subjects with a ≥ 10% change in the body weight during the study period, it should be regulated. In subjects weighing ≥100 kg, it should be calculated, regarding the body weight as 100 kg.

In this clinical study, 1.8 mg/kg of SGN-35 is administered to 6 children as Cohort 1. Based on the incidence of DLT during the DLT evaluation period, the tolerance of the dose/administration method is evaluated. If DLT is observed in ≤1 of the 6 children, 1.8 mg/kg of SGN-35 should be regarded as tolerable. On the other hand, if DLT is observed in 2 of the 6 children, a shift to Cohort 2 may be promoted. In Cohort 2, 3 subjects are added, and 1.8 mg/kg of SGN-35 is administered. If there is no DLT in the 3 subjects, 1.8 mg/kg of SGN-35 should be regarded as tolerable. However, if the third episode of DLT appears in Cohort 2, no patient will be newly registered.

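### The day-1 censoring sentence in the PFS definition makes no exception for death and conflicts with the event definition in the same paragraph

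*Protocol article*

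**What the plan says.** All the text at issue is in the End points section of the protocol article, under the secondary endpoints PFS and EFS.

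- **PFS event.** "PFS refers to a period from the first day of administration until the first day of PD evaluation or the day of death". The sentence goes on to cover death whatever the factor behind it and to take the earlier of the two dates. It attaches no imaging condition to death.
- **PFS censoring.** The next sentence begins "With respect to data on PFS in subjects who continued study participation until analysis without showing PD" and adds two further groups: children given other anti-tumor treatment, and children excluded from the study before response evaluation. Their censoring date is the last image on which progression was ruled out.
- **PFS without imaging.** The paragraph ends: "Subjects in whom image assessment after initial administration was not conducted, is censored at day 1". Nothing limits this to children who are alive.
- **EFS.** "Events include death, progression of disease, secondary cancer, and toxicity-related discontinuation". Its general censoring rule is conditional: "If there are no events, the subject is censored at the final day of observation".

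The Efficacy endpoints section assigns the Kaplan-Meier method with Greenwood intervals to response duration, PFS and EFS.

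**The concern.** A child who dies after the first dose but before any follow-up image falls under two PFS rules that give different answers: an event on the day of death, or censoring at day 1. No order of precedence is given. A programmer who treats the last sentence as the specific rule overriding the general one would take the child out of the risk set at the origin, and the curve would not fall for that death. The same death would still be an EFS event, so the two curves would treat one child differently.

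A death this early is among the worst outcomes the endpoint is meant to record, and in a trial of six to nine children a single reclassified child moves the curve visibly. The situation is foreseeable. The children have relapsed or refractory disease, and the Follow-up section itself names death among the reasons why scheduled assessments may not take place.

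**Working it through.** The article gives no PFS estimate or expected event count, so there is no planned figure to reproduce. The check has three parts.

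**1. The two definitions side by side, for a child who dies before any post-dose image**

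| Rule | Condition written in the text | Result for this child |
|---|---|---|
| PFS event definition | PD or death, earlier date | Event on day of death |
| PFS day-1 sentence | No post-dose image | Censored at day 1 |
| EFS event definition | Death is listed | Event on day of death |
| EFS general censoring | Only if no event | Does not apply |

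Only the PFS day-1 sentence lacks a condition that would keep it from applying to a child with an event.

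**2. Size, if the day-1 sentence is applied literally**

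Inputs: n = 6 ("Six pediatric patients will be enrolled in this study", Abstract, Methods), or n = 9 if the second cohort opens ("In Cohort 2, 3 subjects are added, and 1.8 mg/kg of SGN-35 is administered", Treatment methods). All treated children are assumed to be in the analysis.

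Suppose k children die before any scan and before any other event or censoring. Counted as events, they multiply the Kaplan-Meier curve by (n − k)/n. Censored at day 1, they multiply it by 1. Hence

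S_counted(t) = [(n − k)/n] × S_literal(t), and the gap is (k/n) × S_literal(t).

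Just after one such death (k = 1, S_literal = 1):
- n = 6: 5/6 = 83.3% against 100%, a gap of 16.7 points.
- n = 9: 8/9 = 88.9% against 100%, a gap of 11.1 points.

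Later in follow-up the gap shrinks in proportion to S_literal. The event times below are assumptions for illustration: death at day 20 without a scan, PD at days 100 and 200, all others censored at day 365. PFS after day 200 is then:
- n = 6, death counted: 5/6 × 4/5 × 3/4 = 50.0%. Literal rule: 4/5 × 3/4 = 60.0%. Gap 10.0 points (0.600/6).
- n = 9, death counted: 8/9 × 7/8 × 6/7 = 66.7%. Literal rule: 7/8 × 6/7 = 75.0%. Gap 8.3 points (0.750/9).

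The Greenwood standard errors at that time for n = 6 are 20.4 points (death counted) and 21.9 points (literal), so the gap is about half a standard error.

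**3. How likely the situation is**

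The documents give no rate of death before the first scan. With an assumed per-child rate p, the chance of at least one such death is 1 − (1 − p)^n:

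| Assumed p | n = 6 | n = 9 |
|---|---|---|
| 2% | 11% | 17% |
| 5% | 26% | 37% |
| 10% | 47% | 61% |

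These rates only show the range. Eligibility requires an expected survival of at least three months and performance status 0 to 2, which makes such a death less likely but does not exclude it. The article does not show the imaging schedule, so the length of the window before the first scan cannot be judged.

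**The case against.** The strongest reply is that the day-1 sentence should be read in sequence. It follows directly after the list of children to be censored at their last progression-free image, and its natural job is to supply a date for those children when no such image exists. By ordinary convention, censoring applies only to subjects without an event. On that reading the death counts and nothing is biased. The EFS text, which counts death without an imaging condition, can be cited in support.

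This reading is reasonable and may well be what the authors meant. It rules out a stronger inference that a reader might draw: that the plan removes early deaths and PFS is overstated. The text does not establish that. Overstatement needs both the literal reading and at least one such death. Nor is the disagreement between PFS and EFS a separate defect, since it follows from the literal reading alone.

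The reply does not make the text unambiguous. The authors wrote the no-event condition into EFS censoring but not into this sentence. Nor is this a detail left to an unseen analysis plan: it is a stated rule that conflicts with a stated definition, and a plan that copied it would carry the conflict over.

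The objection on consequences also stands. The primary endpoints are DLT and adverse events, tolerability is decided on DLT counts, and no threshold or comparison is attached to PFS. The death would still appear in EFS, and a drug-related fatal toxicity in the DLT period would also appear in the primary endpoints.

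**Conclusion.** The point holds as an internal conflict in the PFS definition: one paragraph gives two answers for a child who dies before any post-dose image. If the day-1 sentence is applied literally, any resulting error is upward. For one such death it is at most 16.7 points with six children or 11.1 points with nine, immediately after the death, and smaller once other events have occurred. If the event definition governs, or if no such death occurs, the error is zero. The later-time figures rest on assumed event times.

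Severity is minor to moderate. The wording can produce a wrong estimate for the most serious outcome and should be settled before analysis, but PFS is a descriptive secondary endpoint and no decision in the article rests on it.

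**What to change.** Replace the last sentence of the PFS definition with wording such as: *Subjects with no image assessment after the first administration who have not died are censored at day 1. Death from any cause without prior PD is a PFS event on the date of death, whether or not any post-dose image was obtained.* Carry the same wording into the analysis plan if it repeats the definition.

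The cost is one clause. Dates of death are already required for PFS and EFS, so no data collection, visit or sample size changes.

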### Efficacy assessment method

The anti-tumor effects of SGN-35 are evaluated only in patients with measurable lesions according to the Revised Response Criteria for Malignant Lymphoma [13] based on the results of cervical, thoracic, abdominal, and pelvic computed tomography (CT) and positron emission tomography (PET), which were performed at the points established in the study protocol. At each point, the treatment response is assessed as CR, PR, SD, or PD. Lesions meeting the following criteria are regarded as measurable:Nodular masses of lymph nodes or extranodular organs evaluated as lymphoma on CTThe lesion can be clearly measured in two intersecting directions on cross sections of CT.The maximum diameter exceeds 1.5 cm on cross sections of CT.Positive findings on FDG-PET.

Among measurable lesions, 6 lesions at maximum in the order of maximum diameter on cross sections of CT should be selected as target lesions regardless of nodular or extranodular lesions.

If subjects are positive for bone marrow infiltration on baseline assessment, follow-up by bone marrow aspiration or biopsy may be necessary. To evaluate the treatment response as CR, subjects must be negative for bone marrow infiltration. If morphological examination-based evaluation is impossible, the results of examination using immunostaining should also be considered.

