### Efficacy endpoints

The ORR, CR rate, and their 95% confidence interval will be calculated in the FAS. To estimate the response duration, PFS, and EFS, the Kaplan-Meier method will be used. Their 95% confidence interval will be calculated with Greenwood’s formula.

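### EFS counts stopping for drug toxicity as an event but censors switches and withdrawals for inadequate response without recorded progression, which probably overstates the Kaplan-Meier EFS

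*Protocol article*

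**What the plan says.** The EFS definition is under End points in the protocol article. Its events are: "Events include death, progression of disease, secondary cancer, and toxicity-related discontinuation". The toxicity item is explained as follows: "Toxicity-related discontinuation refers to the discontinuation of this clinical study related to adverse events of which the relationship with this drug cannot be ruled out". Time runs to whichever event comes first: "EFS refers to the interval from the first day of administration until the earliest day of event appearance".

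Two sentences then govern children who leave without an event. On transplantation and withdrawal: "If it is discontinued due to transplantation or withdrawal in the absence of events, they are censored at the day of study discontinuation". On other therapy: "If subjects receive new anti-tumor treatment other than stem cell transplantation, they are censored at the start of the treatment".

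Efficacy assessment method allows a result that is neither response nor progression: "At each point, the treatment response is assessed as CR, PR, SD, or PD". Efficacy endpoints fixes the estimator, "To estimate the response duration, PFS, and EFS, the Kaplan-Meier method will be used", and the interval, "Their 95% confidence interval will be calculated with Greenwood’s formula".

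**The concern.** By counting a drug-related stop, EFS goes beyond disease status and becomes partly a measure of treatment failure. Giving up SGN-35 because of harm is an event. Giving it up because it does not work well enough is not, unless progression has been recorded first. The eligibility criteria, by contrast, accept lack of CR or PR after earlier treatment as one way of being refractory, so the protocol itself recognises non-response as a form of failure.

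Kaplan-Meier treats censoring as uninformative. A child moved to other therapy, or withdrawn, because of inadequate response probably has a worse outlook than the children who stay on SGN-35. Removing that child from the risk set would then make EFS look better than it is. The trial has a single arm, so no comparison group carries the same bias, and with six children one or two such cases visibly move the curve.

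**Working it through.** The article gives no EFS rate, target or threshold, so there is no figure to reproduce. The six children, plus three if Cohort 2 opens, are tied to the DLT rule. All switch counts, times and rates below are assumptions.

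**1. Tracing one child through the rules.** Take a child with SD, no PD and no drug-related adverse event, who leaves SGN-35 for inadequate response.
- None of the four listed events applies.
- If new non-transplant treatment starts first, the child is censored on its start date.
- If the child is withdrawn first, censoring is on the day of study discontinuation.
- The same child stopping for a drug-related adverse event would be an event.
- The same child with progression recorded before leaving would also be an event, because EFS ends at the earliest event.

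**2. What the estimator does.** S(t) is the product over event times of (1 − d/n), where d is events and n is children at risk. A censored child lowers later n without ever adding to d. Counting the switch as an event is the opposite extreme: it treats the child as failing on that day. If children who leave for inadequate response have at least the risk of those who stay, the two figures bracket the answer.

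**3. Six children, assumed data.** PD at months 2 and 5, switches for inadequate response at months 3 and 4, two children event-free at month 6.
- As defined: at month 2, 1 event among 6; at month 5, 1 event among 3. EFS = 5/6 × 2/3 = 0.556.
- Switches as events: 2 of 6 remain event-free. EFS = 2/6 = 0.333.
- Greenwood SE as defined: 0.556 × √(1/(6×5) + 1/(3×2)) = 0.556 × √0.2 = 0.248. The 95% interval is 0.556 ± 1.96 × 0.248, about 7% to 100% after cutting at 100%.

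**4. Varying the number of switches.** Six children, PD at month 3, toxicity stop at month 5, the rest followed to month 12.

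| Switches for inadequate response | 12-month EFS as defined | Switches as events |
|---|---|---|
| None | 4/6 = 66.7% | 66.7% |
| One (month 2) | 4/5 × 3/4 = 60.0% | 3/6 = 50.0% |
| Two (months 2, 4) | 4/5 × 2/3 = 53.3% | 2/6 = 33.3% |

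If switches are the only occurrences, EFS as defined stays at 100% with one, two or three switches, against 83.3%, 66.7% and 50.0% when they count.

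**5. Without small-sample noise.** Assume constant hazards: λ = −ln(S)/12 for listed events, and μ for switches, chosen so that μ/(μ+λ) × (1 − exp(−12(μ+λ))) equals the proportion p switching by month 12. EFS with switches as events is exp(−12(λ+μ)).

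| 12-month EFS as defined | p = 10% | p = 20% | p = 30% |
|---|---|---|---|
| 50% | 43.1% | 36.4% | 29.8% |
| 70% | 61.7% | 53.5% | 45.3% |

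**6. Chance that it arises at all.** The probability of at least one such switch among six children is 1 − (1 − p)^6: 47%, 74% and 88% for p = 10%, 20% and 30%.

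**The case against.** The rule is explicit and workable, and PFS also censors at other anti-tumor treatment. EFS is the last of six secondary endpoints in a phase I study whose only decision rule uses DLT. The interval in step 3 is so wide that 33% lies well inside it. A sensitivity analysis is commonly left to a SAP, which is not shown. All of this limits the weight of the point. It does not remove a bias that follows from a rule the article itself states, and a wide interval does not correct a shifted estimate.

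Three stronger readings are tempting, and the documents do not support them.

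- **That every censored switch pushes EFS upward.** The article gives neither the reasons for switching nor their frequency. Its Background describes chemotherapy combined with low-dose radiotherapy as part of treatment, so a responding child could receive further therapy without having failed SGN-35. Counting that child as an event would lower the figure without correcting anything. A lower figure after recoding is therefore not by itself evidence of bias.
- **That clinical worsening before a scan always escapes EFS.** The list of events names progression without an imaging condition in that sentence. PD is assessed from CT and PET elsewhere, so this is arguable, but clinical progression may already count. The clear gap is leaving SGN-35 for inadequate response in stable disease.
- **That EFS adds little to PFS for children who switch.** A child who stops for drug toxicity and then changes therapy is an EFS event but not, on that ground, a PFS event. For switchers without any event the censoring dates also differ: last imaging for PFS, start of treatment for EFS.

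Turning every new treatment into an event would thus be too broad. Changing only the sentence on new treatment would be too narrow, since a child withdrawn for lack of effect before other therapy starts is already censored by the sentence before it.

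**Conclusion.** The point holds for a limited group: children who start new non-transplant anti-tumor treatment, or withdraw, because of inadequate response and without a recorded event. For them the censoring is probably informative and would overstate EFS. This rests on one assumption that the documents cannot confirm, namely that such children carry a higher later risk than those who remain.

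The actual size is unknown. In the six-child illustrations the gap is 10 to 17 points with one such switch and 20 to 33 points with two; with none it is zero. The tolerability conclusion and the DLT and adverse event results do not depend on it. This is an inexpensive improvement to a secondary efficacy figure, not a defect in the trial's main result.

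**What to change.** Keep the stated EFS definition if preferred, and add:

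- a second Kaplan-Meier EFS estimate in which the start of new non-transplant anti-tumor treatment, or withdrawal, for inadequate response is an event on its date (the earlier date if both occur);
- a listing of the reason for every such switch or withdrawal.

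Leave the handling of transplantation, and of consolidation given to responders, unchanged in both estimates. If the SAP already provides this, nothing more is needed.

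The start and discontinuation dates are already needed for the present rule, so the cost is one further Kaplan-Meier run and a short listing. The downsides are that the second figure may be lower and that someone must classify each reason; a classification rule written before the data are reviewed would keep that from being arbitrary.
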